### Sample size calculation

Compliance with the active ERAS elements is described in literature. The study population and data analyses of the study of Thorn et al. shares similarities with our proposed study [11]. Therefore, we used results from the study of Thorn et al. as references values to calculate the sample size. We assumed that the two ERAS elements ‘early mobilization’ and ‘adequate intake’ depended the most on participation of the patient and to which a mobile application that stimulates the patient to mobilize and to follow a normal diet, could contribute the most. The average compliance of these two elements is 57% [11]. We hypothesize that the overall average compliance percentage of the selected active elements in the APPtimize study group will increase to 62%. Although an increase of 5% might not seem clinically relevant, we expect that the some individual ERAS elements, such as early mobilization, even show a greater increase and therefore enhance clinical utility. Through a sample size calculation with 90% power, a 2-sided alpha of 0.05, and a standard deviation of 9, we estimated that 70 participants per study group are needed. A loss to follow-up of 10% was estimated. Therefore, the total target sample size is 156 participants ((2 × 70) / 0.9 = 156).

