### Outcomes

The primary outcome is the overall average compliance to the selected active ERAS elements (Table 2). Since the application is patient-centred and focusses on empowering patients to get in control of their own health, the PROMs, such as health related quality of life and patient satisfaction, are considered important secondary outcome parameters. Other secondary outcomes include postoperative outcome parameters (e.g. complications), gastro-intestinal recovery (e.g. time to passage of stool), activity and pain measurements. Table 5 describes all study outcomes and how and when these will be measured.

**Table 5 Tab5:** Time points and measurements

Enrolment		T0	T1	T2	T3	T4	T5	T6	T7	Registered in/with:
	Eligibility screen	x								
	Informed consent	x								
	Allocation	x								
Interventions		T0	T1	T2	T3	T4	T5	T6	T7	
Intervention group	Download mobile application	x								
	Wear activity tracker		O	O	O	O	O	O		
Control group	Wear activity tracker		O	O	O	O	O	O		
Data measurements		T0	T1	T2	T3	T4	T5	T6	T7	
Baseline characteristics	General characteristics	x								Sex, age, ASA, BMI, smoking, alcohol intake
	Disease related characteristics	x								Disease, operation
	eHealth literacy assessment	x								eHEALS
Protocol compliance *(as reported by patients)*	1. Cessation of smoking and excessive intake of alcohol	x								Y/N questions in app or with paper form
	2. Preoperative nutritional screening and, as needed, assessment and nutritional support	x								Y/N questions in app or with paper form
	3. Preoperative carbohydrate treatment			x						Y/N questions in app or with paper form
	4. Preoperative prophylaxis against thrombosis			x						Y/N questions in app or with paper form
	5. Early mobilization (day of surgery)				O	O				Y/N questions in app or with paper form
	6. Early intake of oral fluids and solids (offered the day of surgery)				O	O				Y/N questions in app or with paper form
	7. Early removal of urinary catheters and intravenous fluids (morning after surgery)					O				Y/N questions in app or with paper form
	8. Use of laxatives					O				Y/N questions in app or with paper form
	9. Intake of protein and energy-rich nutritional supplements					O				Y/N questions in app or with paper form
	10. Prepare for early discharge					O				Y/N questions in app or with paper form
Postoperative data ≤30 days *(retrospective collection)*	Length of hospital stay								x	EHR
	Overall morbidity ≤30 days								x	EHR

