Potential bias could occur due to the diversity of the study participants regarding to their age, diverse socio-economic status, and different types of colorectal disease. For example, one might suggest that elderly participants could affect study results as some will not be able to work with the application and activity tracker correctly. In our belief, elderly participants should be very capable of using the mobile application and activity tracker. However, to minimize these effects of a selection bias, we chose a randomized study design. Finally, it is reckoned that by distributing activity trackers to patients of the control group and letting them fill out a daily diary, a more active participation to the ERAS care pathway could occur. Subsequently, this will result in a decreased compliance difference between the two study groups. However, if a significant difference of the primary outcome compliance will be found, it even further emphasizes the clinical relevance of a patient-centred mobile application.

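### The 5-point planning difference sets a ten-element target against a two-element reference, so the stated 90% power is not tied to the primary outcome.

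*Protocol article*

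**What the plan says.** The Outcomes section defines the endpoint: "The primary outcome is the overall average compliance to the selected active ERAS elements (Table 2"). Table 2 lists ten elements. Data analyses scores each as completed or not and averages the completion percentages, which I read as equal weights.

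The Sample size calculation starts from two of these elements: "We assumed that the two ERAS elements ‘early mobilization’ and ‘adequate intake’ depended the most on participation of the patient". Their mean in the cited study is the reference: "The average compliance of these two elements is 57% [11"]. The target follows in the next sentence: "We hypothesize that the overall average compliance percentage of the selected active elements in the APPtimize study group will increase to 62" percent. The authors add that some single elements, such as early mobilization, may gain more than 5 points, but give no figure. The remaining inputs are 90% power and "a 2-sided alpha of 0.05, and a standard deviation of 9", leading to 70 per group and, with 10% loss to follow-up, 156 in total.

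The Discussion expects the tracker and daily diary to make control patients more active in the pathway: "Subsequently, this will result in a decreased compliance difference between the two study groups".

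**The concern.** The 57% and the 62% describe different scores. The first averages two elements, picked because they depend most on the patient. The second averages ten, of which Table 1 marks five as Active/Passive with a surgeon or nurse as the responsible or co-responsible professional (nutritional screening, carbohydrate treatment, thrombosis prophylaxis, catheter and infusion removal, discharge preparation).

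Only the difference and the SD enter the sample-size formula, but the difference is itself 62 minus 57. If the control mean of the ten-element score is not 57%, then either the difference is not 5 points or the target is not 62%. The SD has the same gap: no source is named, and the article does not say whether it belongs to the two-element or the ten-element average.

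This paragraph is the article's only justification of the trial's size. At stake is whether 156 patients give the stated power on the outcome that will be tested.

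**Working it through.** **Inputs.** From the Sample size calculation: reference 57%, target 62%, SD 9, two-sided alpha 0.05, power 90%, loss 10%. From Table 2 and Data analyses: ten elements, simple average. From Group allocation and blinding: 1:1 ratio.

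**1. The plan's own figure.** n per group = 2 × SD² × (1.960 + 1.282)² / difference² = 2 × 81 × 10.51 / 25 = 68.1, so 69 by the normal approximation. The t-based calculation gives 69.06, so 70. Total: 140 / 0.9 = 155.6, so 156. Power at 70 per group is 90.4% (t-based). The stated figures reproduce.

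**2. From element gains to the overall gain.** With equal weights, overall gain = (2 × gain on the two reference elements + 8 × mean gain on the other eight) / 10. The standard error of the group difference is 9 × √(2/70) = 1.52 points. With a gain of 5 points on the two elements:

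| Mean gain on the other eight | Overall gain | Power, 70 per group, SD 9 |
|---|---|---|
| 0 | 1.0 | 10% |
| 1 | 1.8 | 22% |
| 2 | 2.6 | 40% |
| 3 | 3.4 | 60% |
| 4 | 4.2 | 78% |
| 5 | 5.0 | 90% |

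If only the two elements respond, each must rise by 5 × 10 / 2 = 25 points (57% to 82%) to give 5 overall. If adequate intake covers Table 2 items 6 and 9, three elements carry the effect. A 5-point gain on those three alone is 3 × 5 / 10 = 1.5 points overall, with about 17% power.

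**3. The control mean (illustration).** The Background quotes pooled adherence of 69% before and 53% after surgery. These rates cover active and passive elements together, so they are only a rough guide. Applied to the four preadmission and preoperative items and the six postoperative items of Table 2, they give (4 × 69 + 6 × 53) / 10 = 59.4%. A rise to 62% is then 2.6 points, with about 40% power. The mean could also lie lower, because nutritional screening is not part of usual care at these sites (Content development).

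**4. The SD (assumption).** The article gives neither element rates nor correlations. For a per-patient average of ten independent yes/no items, SD = 100 × √(Σ p(1 − p)) / 10. For a 5-point difference (normal approximation):

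- all ten at 57%: SD 15.7, 47% power at 70 per group, 207 per group needed for 90%;
- two at 57% and eight at 90%: SD 11.0, 77% power, 102 per group;
- all ten at 90%: SD 9.5, 88% power, 76 per group.

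An SD near 9 is therefore possible, but it depends on element rates that the article does not state.

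**5. Control drift (assumption).** If the control mean rises by 1 or 2 points and the app arm stays at its target, the difference is 4 or 3 points. Power is then about 75% or 50% (SD 9).

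**The case against.** A reader might infer that the design dilutes any effect five-fold. The documents do not support that. A fall from 5 points to 1 needs exactly no effect on eight elements, and the protocol assumes no such thing. All ten elements are in the app, Table 3 schedules notifications on nutrition, smoking, alcohol and the preoperative drink as well as daily goals, and the two elements are only those where the app is expected to contribute most.

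A reader might also infer that the sample size is miscalculated or that the planned effect lies on the wrong endpoint. Neither holds. The 5 points are stated for the overall average, and 70 per group is correct for them. Larger gains on some elements are foreseen: 10 points on two and 3.75 on eight would give (20 + 30) / 10 = 5 overall. Changing the 57% while holding the difference and the SD would leave the sample size as it is.

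Element-level reasoning may also exist in the cited study or the full protocol, which are not shown, and the Discussion is open about control drift.

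All of this limits the size of the problem. It does not remove the mismatch, because the article itself obtains the 5 points by setting a ten-element target against a two-element reference and shows no element gains that average to 5.

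**Conclusion.** The point holds as a mismatch between the planning reference and the endpoint. The 90% power is right for a difference of 5 and an SD of 9, but neither number is tied to the ten-element score. How much power is lost, if any, depends on element rates and effects that the article does not give. Under equal weights and SD 9, with the two reference elements gaining 5 points, power runs from about 10% if the other eight do not move to 90% if they gain as much. The documents do not show that the trial is underpowered; they leave its power on the primary outcome unsupported.

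**What to change.** In the sample-size paragraph, replace the 57% reference with an assumed control mean for the ten-element score. Build it from an assumed control rate and app effect for each Table 2 element, and average these to the composite difference. Use an SD for that same score and name its source. Allow for the rise in control compliance that the Discussion expects. Then restate the power that 156 patients (about 70 evaluable per group) give.

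Keep the ten-element primary outcome. Moving it to the two reference elements would make calculation and endpoint agree, but it abandons the stated objective and could lower power. If two independent yes/no items at 57% are assumed, the SD is 100 × √(0.57 × 0.43 / 2) ≈ 35 points. A 5-point gain then has about 13% power at 70 per group.

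The cost is a rewritten paragraph and a short table of assumptions; data collection had not begun when the protocol was submitted. The downside is that the restated power may be less favourable than 90%.

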### Data analyses

Statistical analyses of any difference between the two study groups will be performed using SPSS for Windows version 25 or higher (SPSS Inc. Chicago, IL). Data will be analysed according to intention to treat protocol. If applicable, missing data will be imputed. Baseline characteristics will be summarized using descriptive statistics and compared between the intervention and control groups. Continuous data will be reported as mean and standard deviation in case of normal distribution and as median 95% confidence intervals in case of non-normal distribution. Normality of the data distribution will be analysed by visually inspecting the histograms and Kolmogorov-Smirnov test. Comparative analysis will be done using a two-sided t-test in case of normal distribution and by means of the Mann-Whitney U test in case of non-normal distribution. *P*-values of ≤0.05 will be considered statistically significant.

Categorical data will be displayed as numbers and percentages and analysed using a Chi-square test.

Investigational site, surgical procedure, age, and score on the eHealth literacy test will be taken into account as covariates in the adjusted analyses. Intended subgroup analyses will be conducted for the surgical procedure.

To estimate the primary outcome, the overall average compliance to the selected active ERAS elements, the elements will be scored as ‘completed’ or ‘not completed’ (dichotomous), as described by the ERAS protocol. For example, the urine catheter should be removed on day one after surgery. If this could not take place, the element was scored as ‘not completed’. For both the intervention and control groups, the proportion of completion of each individual active element will be calculated. The overall compliance is an average of the individual completion percentages. The protocol compliance is a continuous variable and will be reported as mean and standard deviation in case of normal distribution and as median and 95% confidence intervals in case of non-normal distribution.

The relation of the use of the application with the secondary outcomes mentioned in Table 5 will be examined with a linear regression.

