### Investigational intervention

#### Content development

A consensus meeting was organized with a multidisciplinary team of caregivers, representing both Amsterdam UMCs’ locations. Both locations practice almost all the elements from the 2012 ERAS society recommendations for colorectal surgery as part of their ‘care as usual’ except for ‘nutritional screening’ and ‘chewing gum as a laxative’. [9] Active ERAS elements, elements that depend on patient involvement, were included in the application. The multidisciplinary team of caregivers evaluated the ERAS elements for their eligibility to be included in the application. Although ‘nutritional screening’ was not part of current ‘care as usual’, the multidisciplinary team thought it would be useful to include this element in the application. Table 2 displays all elements that were included in the application. In ‘Additional file 1’, one can find the functional design of the application. The functional design illustrates the workflow through the application and the basic layout. After the first version of the application will be developed, ‘patient experts’ will be invited to test the application and review the content of the application.

**Table 2 Tab2:** ERAS elements in the APPtimize application

Preadmission	
1. Cessation of smoking and excessive intake of alcohol	
2. Preoperative nutritional screening and, as needed, assessment and nutritional support	
Preoperative	
3. Preoperative carbohydrate treatment	
4. Preoperative prophylaxis against thrombosis	
Postoperative	
5. Early mobilization (day of surgery)	
6. Early intake of oral fluids and solids (offered the day of surgery)	
7. Early removal of urinary catheters and intravenous fluids (morning after surgery)	
8. Use of laxatives	
9. Intake of protein and energy-rich nutritional supplements	
10. Prepare for early discharge	

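### The two-level primary score has no place for patients to whom smoking and alcohol cessation does not apply, so they count as success or failure whatever the app does

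*Protocol article*

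**What the plan says.** All references are to the protocol article.

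- **Scale.** Under Data analyses, "the elements will be scored as ‘completed’ or ‘not completed’ (dichotomous), as described by the ERAS protocol".
- **Example.** The one illustration is a urinary catheter that should be out on day one after surgery: "If this could not take place, the element was scored as ‘not completed".
- **Aggregation.** For each group "the proportion of completion of each individual active element will be calculated", and then "The overall compliance is an average of the individual completion percentages". No denominator restricted to applicable patients is mentioned.
- **Capture.** In Table 5 (Outcomes) each of the ten elements is registered by "Y/N questions in app or with paper form".
- **Content.** Table 2 (Content development) lists "1. Cessation of smoking and excessive intake of alcohol" and "2. Preoperative nutritional screening and, as needed, assessment and nutritional support" among the ten.
- **Baseline data.** Table 5 collects "Sex, age, ASA, BMI, smoking, alcohol intake" at T0, which its legend defines as the moment of randomisation. The compliance entry for element 1 is also marked at T0 and nowhere else.
- **Eligibility.** Study population does not limit entry to smokers or heavy drinkers.

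**The concern.** A patient who neither smokes nor drinks excessively has nothing to stop. Asked a yes/no question about cessation, that patient could truthfully answer either way, and the scale turns one answer into a success and the other into a failure. Neither carries information about the app.

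Three things are at stake:

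- the absolute compliance figure depends on an unstated coding choice;
- one of the ten elements cannot respond to treatment in these patients, which dilutes the difference;
- the intervention group answers in the app and the control group on paper, so the two forms could draw different answers from the same kind of patient.

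**Working it through.** **The plan's own figure.** Inputs from Sample size calculation: 57% versus 62% (difference 5 points), SD 9, two-sided alpha 0.05, power 90%, loss 10%.
- Normal approximation: n = 2 × [9 × (1.960 + 1.282) / 5]² = 68.1, so 69 per group. The t-test version gives 70 per group (power 0.904).
- 2 × 70 / 0.9 = 155.6, so 156.

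The stated 70 and 156 reproduce and are not in question.

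**Assumptions for the rest.** The article does not give the share a of patients to whom element 1 applies; I take a = 0.5 to 0.2, so s = 1 − a = 0.5 to 0.8 have nothing to stop. I take 57% completion for every applicable element, a 5-point gain on every applicable element, and independent elements. The 57% is borrowed: in the article it is the average of two elements only.

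**Level, compared with scoring completed over applicable elements.** One element in ten is worth 10 points.
- Inapplicable patients scored not completed: fall = 10 × s × 0.57 = 2.9 (s = 0.5) to 4.6 (s = 0.8) points.
- Scored completed: rise = 10 × s × 0.43 = 2.2 to 3.4 points.

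**Attenuation.** Difference = 5 × (1 − s/10) = 4.75 (s = 0.5) to 4.60 (s = 0.8) points, under either coding.

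**Standardised effect.** Variance of one element: 0.57 × 0.43 = 0.2451. In squared percentage points:
- current scoring: 100 × [9 × 0.2451 + p₁(1 − p₁)], where p₁ = 0.57a if inapplicable patients are scored not completed, and s + 0.57a if completed;
- completed over applicable: 10,000 × 0.2451 × (a/10 + s/9).

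| a | Scoring | Difference | SD | Effect/SD | Gain from applicable scoring |
|---|---|---|---|---|---|
| 0.5 | not completed | 4.75 | 15.52 | 0.306 | 1.6% |
| 0.5 | completed | 4.75 | 15.41 | 0.308 | 0.8% |
| 0.5 | applicable only | 5.00 | 16.08 | 0.311 | – |
| 0.2 | not completed | 4.60 | 15.19 | 0.303 | 1.1% |
| 0.2 | completed | 4.60 | 15.11 | 0.304 | 0.6% |
| 0.2 | applicable only | 5.00 | 16.34 | 0.306 | – |

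The gain is under 2% throughout. This simple model gives SDs of 15-16, not the planned 9, so only the ratios should be read from it.

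**Different answering by arm.** If inapplicable patients said yes 10 to 20 percentage points more often in one arm (assumed), the spurious difference would be 10 × s × 0.10 to 0.20, that is 0.5 (s = 0.5, 10 points) to 1.6 (s = 0.8, 20 points).

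**The case against.** The strongest reply is that the article does not state the rule one might read into it. The catheter is an applicable element that failed, and scoring it as not completed is right. A reader might infer that every inapplicable element is likewise scored as a failure; the text does not say so. It also refers item scoring to the ERAS protocol and does not show the wording of the questions, so a full protocol or form could contain a rule. That stands. What remains is that the article itself fixes two levels, yes/no capture and a plain average for the primary outcome, and that leaves no place for these patients.

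Other parts of the reply also stand:

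- **Element 2 is weak support.** Every patient can be screened, and the wording already makes support conditional. A screened patient who needs no support has met it.
- **The level shift cancels on average.** Randomisation balances the inapplicable share in expectation. Moving all these patients from not completed to completed shifts the mean by 10 × s = 5 to 8 points, and a reader might set that beside the 5-point target. But that compares two codings with each other, and a level with a between-arm contrast.
- **Chance imbalance is not bias.** It is already in the standard error of the t-test (9 × √(2/70) = 1.52 points).
- **A serious power loss is not shown.** Holding the SD at 9, a 4.75-point difference has 87% power at 70 per group. But an item with a fixed score in these patients also contributes less variance, and the article sets its 5 points for the overall average, so weakly responsive elements may already be allowed for.
- **Comparison with the 57% reference** is limited under any coding, because that figure covers two elements.
- **A not-applicable rule alone does not make element 1 responsive.** As tabulated it is recorded only at randomisation, so it could not reflect the app even in smokers.

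**Conclusion.** The point holds in a limited form. The primary score counts patients with nothing to stop as success or failure on element 1, and the article does not say which. Under the stated assumptions (element 1 applicable to 20-50%, 57% completion per element), the reported level is about 3-5 points too low or about 2-3 points too high, and a 5-point effect appears as about 4.6-4.75. The effect on power is small.

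The documents do not show a systematic bias between arms. It would arise only if the app and the paper form led these patients to answer differently, which is possible with two modes of capture but not demonstrated. Severity is minor to moderate: the case for changing the score is that its level and meaning are unclear and the remedy is cheap.

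**What to change.** 1. Define each patient's score as completed elements divided by applicable elements, and name this patient-level score as the primary outcome. Once denominators differ, it no longer equals the average of the ten element percentages exactly.
2. Decide applicability of element 1 only from smoking and alcohol intake recorded at T0, so that it cannot depend on arm. State in advance what counts as excessive intake for this purpose.
3. Keep the not-completed score for applicable elements that failed, such as a catheter not removed on day one.
4. Count element 2 as met when screening was done and no support was needed.
5. Record element 1 again after the app has been used. With the T0 entry alone, the item cannot reflect the intervention in the patients to whom it applies.
6. Report the all-ten score as a sensitivity analysis, with the coding of inapplicable patients stated.

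The cost is a few sentences of scoring rules and one later entry for element 1 in the app and diary. The T0 data are already collected, and the article says data collection had not begun when it was submitted. The small downside is that denominators differ slightly between patients (9 or 10).

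### The primary compliance score is described by element within each arm although the sizing needs a score per patient, and a normality pre-test would probably replace the 5-point mean difference with medians that often do not move

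*Protocol article*

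**What the plan says.** All of this is in the protocol article.

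- **Scoring (Data analyses).** Each element is binary: "the elements will be scored as ‘completed’ or ‘not completed’ (dichotomous), as described by the ERAS protocol". Table 2 lists ten elements, ending with "10. Prepare for early discharge".
- **Building the score (Data analyses).** "For both the intervention and control groups, the proportion of completion of each individual active element will be calculated"; then "The overall compliance is an average of the individual completion percentages".
- **Type of variable (Data analyses).** "The protocol compliance is a continuous variable and will be reported as mean and standard deviation in case of normal distribution". The alternative is a median with a 95% confidence interval.
- **Choice of method (Data analyses).** "Normality of the data distribution will be analysed by visually inspecting the histograms and Kolmogorov-Smirnov test". Then: "Comparative analysis will be done using a two-sided t-test in case of normal distribution and by means of the Mann-Whitney U test" if the data are not normal.
- **Sizing (Sample size calculation).** Mean compliance of 57% rising to 62%, SD 9, 90% power, two-sided alpha 0.05, 70 participants per group, and 156 in total after 10% loss.

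**The concern.** Two things do not fit together.

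First, the completion proportion of one element exists only across patients. The two sentences that build the score therefore give ten percentages and one average per arm. An arm-level average has no between-patient SD, cannot be checked for normality and cannot enter a t-test. The SD of 9 and the 70 participants per group presuppose a different quantity, a percentage for each patient, which the article does not define.

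Second, once a per-patient score is used, the data decide whether the primary result is a mean difference or a pair of medians. The trial was sized on a mean difference of 5 points. A score made of ten yes/no items moves in 10-point steps, so a normality test is likely to fail for reasons unrelated to whether a t-test is valid. The summary that replaces the mean may be too coarse to show 5 points. The trial could then report a significant p-value beside a median difference of zero.

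**Working it through.** **1. The plan's own figure.** n per arm = 2(z₀.₉₇₅ + z₀.₉₀)² SD²/δ² = 2 × (1.960 + 1.282)² × 81/25 = 68.1, so 69. The exact t-test solution is 69.06, rounded up to 70, and power at 70 per arm is 0.904. Total: 140/0.9 = 155.6, so 156. The stated sample size is reproduced. It is a calculation for a difference in means of a per-patient variable.

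**2. Arm average against patient average.** Let yᵢⱼ be 1 if patient i completed element j. With complete data and the same ten elements for everyone, (1/10)Σⱼ(1/n)Σᵢ yᵢⱼ = (1/n)Σᵢ(1/10)Σⱼ yᵢⱼ. The two constructions give the same point estimate. They differ in the SD, in the unit that is tested, and in the estimate itself once some elements do not apply or are missing.

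**3. Why the gate tends to close.** With a fixed denominator of ten, the score takes the values 0, 10, ..., 100. Take a normal score with mean 57 and SD 9 rounded to this grid. The share at exactly 60 is Φ((65−57)/9) − Φ((55−57)/9) = 0.813 − 0.412 = 0.40. A continuous curve must miss a step of 0.40 by at least half of it, 0.20. The large-sample 5% limits at n = 70 are 0.886/√70 = 0.106 with the Lilliefors correction and 1.358/√70 = 0.162 without it. Both are exceeded.

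**4. Why the medians do not move.** In the same example, the control arm has 0.412 of scores below 60 and 0.813 at or below 60, so its median is 60. With mean 62, the app arm has Φ((55−62)/9) = 0.218 below 60 and Φ((65−62)/9) = 0.631 at or below 60, so its median is also 60.

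**5. Simulation.** 70 per arm, ten binary elements, true means 57% and 62%, 2,000 to 4,000 trials per scenario. The spread of element rates and the correlation within patients are assumptions, since the article gives neither; together they determine the per-patient SD. K-S was run in the first 500 trials of each scenario, counting rejection in either arm. In the varying-denominator rows each element is not applicable with probability 0.10.

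| Denominator | SD | Lilliefors K-S rejects | Uncorrected K-S rejects | Power, t-test | Power, Mann-Whitney | Medians identical |
|---|---|---|---|---|---|---|
| Ten | 8.0 | 100% | 100% | 0.96 | 0.95 | 94% |
| Ten | 9.0 | 100% | not run | 0.91 | 0.90 | 92% |
| Ten | 10.4 | 100% | 100% | 0.79 | 0.78 | 85% |
| Ten | 13.3 | 100% | 95% | 0.61 | 0.59 | 75% |
| Ten | 15.5 | 100% | 71% | 0.46 | 0.44 | 67% |
| Ten | 18.6 | 100% | 35% | 0.36 | 0.35 | 55% |
| Varying | 10.6 | 95% | not run | 0.78 | 0.78 | 11% |
| Varying | 16.4 | 56% | not run | 0.44 | 0.42 | 10% |

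Power falls down the table because the SD rises, not because of the gate. The comparison that matters is between the two power columns within a row. At SD 9 with a fixed denominator, the median difference was exactly 5 in 4% of trials and 10 or more in 5%. With varying denominators it lay between 2.5 and 7.5 in 74% (SD 10.6) and 57.5% (SD 16.4) of trials.

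A separate simulation gave the same picture. Mann-Whitney against t-test power was 0.85 v 0.87 for a normal score of SD 9 rounded to the grid, and 0.47 v 0.50 at SD about 14.6. Medians were identical in 72-91% of trials with a fixed denominator.

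**The case against.** **The text may not mean an arm-level analysis.** A reader might infer that the trial will compare ten element percentages with ten others and so has the wrong unit of analysis. The article does not support that. It calls compliance continuous, gives it an SD and sizes the trial on participants. The sentences on element proportions can be read as describing a group summary, and step 2 shows that they give the same point estimate when data are complete. What stands is a contradiction within the text, not a planned arm-level test.

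**Mann-Whitney would find the effect.** A reader might infer that the non-parametric branch cannot detect 5 points. It can: its power is within about 3 points of the t-test throughout. Only the median summary fails.

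**The gate is not automatic.** Histograms are inspected as well, and no rule says how the two are combined. The version of K-S is not named, and the uncorrected form rejects in 35-100% of fixed-denominator trials. The switch is therefore probable, not certain.

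**The median problem depends on the denominator.** If elements that do not apply are dropped, as the fix below proposes, identical medians become uncommon (about 10%). This is a real limit. The catheter example in Data analyses, where removal that could not take place counts as not completed, points towards a fixed denominator, but the article does not settle the matter. Under either denominator the effect measure still depends on a pre-test.

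**The article is condensed.** A full protocol or analysis plan may hold the per-patient formula. The point here, though, is not an omission: the article states a construction that conflicts with its sizing, and it states the gate as the rule. The covariate-adjusted analyses it mentions are not named as primary, so they do not resolve either issue.

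**Conclusion.** The point holds in a limited form. The description of the primary score and the basis of the sample size do not agree on the unit, and must be reconciled. The normality gate would probably move the trial away from the mean difference on which it was sized: in every trial checked with a fixed ten-element score under Lilliefors-corrected K-S, and in roughly 55-95% if denominators vary. The significance test would hardly change. The reported effect could: identical medians in about 55-94% of trials with a fixed denominator, and about 10% with a varying one, while the true mean difference is 5 points.

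These ranges rest on assumed element rates and correlations, per-patient SDs from 8 to 18.6, and 10% non-applicable elements in the varying case. The sample size arithmetic is correct. Whether SD 9 suits a per-patient ten-element score is a separate question that the article does not answer.

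**What to change.** In Data analyses:

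1. Define compliance for each patient as completed elements / elements applicable to that patient x 100, and say when an element is not applicable rather than not completed.
2. Make the primary estimate the difference in mean per-patient compliance with its 95% CI, from a t-test or a linear model, regardless of any normality test. A linear model can carry the covariates already listed; robust standard errors are optional.
3. Keep Mann-Whitney as a sensitivity analysis and report the element percentages per arm descriptively.

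In Sample size calculation, state that the SD of 9 is meant as the SD of this per-patient score, so that the two sections refer to the same variable.

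The cost is a few sentences. The yes/no items are already collected from each patient, so no data change.
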